### Outcomes assessments

The primary and secondary outcomes will be measured in two main time points: pre- and post-intervention. The pre-intervention assessments of the outcomes will be performed at the first day of the intervention before tDCS stimulation (T
_1_). There will be four time points of post-intervention assessments as T
_2_, T
_3_, T
_4_, and T
_5_ corresponding to the immediately after last session, one hour, one week, and one month after last tDCS session.
Table 2 represents the SPIRIT schematic protocol of the study and timing of the assessments.

**Table 2. T2:** Standard Protocol Items: Recommendations for Interventional Trials of this study.

	Enrolment	Allocation	Pre- intervention	Intervention	Post- intervention			
TIME POINT	*-T _1_*	T _0_	*T _1_*		*T _2_*	*T _3_*	*T _4_*	*T _5_*
ENROLMENT:								
Eligibility screen	X							
Informed consent	X							
*Demographic* *information*	X							
Allocation		X						
INTERVENTIONS:								
*real (anodal and* *cathodal) tDCS*								
*Sham tDCS*								
ASSESSMENTS:								
*Neurological* *and audiological* *assessments*	X							
*Hearing loss* *assessment*	X							
*Primary outcome:* *THI*			X		X			X
*Secondary outcomes:* *loudness*			X		X	X	X	X
*Distress*			X		X	X	X	X
*AEs and Tolerability*					X			

Note: THI: tinnitus handicap inventory; AEs: adverse effects, -T
_1_: one month before intervention, T
_0_: one day before intervention, T
_1_: 5 min before intervention, T
_2_: immediately after last session, T
_3_: at hour after last session, T
_4_: one week, and T
_5_: at month after last tDCS session. Real tDCS refers to anodal and cathodal tDCS groups.

***Primary outcome***. Tinnitus handicap inventory (THI) score will be the primary outcome. The THI is a 25-item questionnaire and commonly used as self-reporting inventory for disabling level of tinnitus. The THI items are grouped into three subscales: Functional (11 items), emotional (9 items), and catastrophic (5 items) subscales. Each item is three point Likert type scale with three alternative assessments: yes (4 points), sometimes (2 points), and no (0 point). The questionnaire yields scores for each subscale and a total score that ranges 0 to 100, where higher score means more severe tinnitus or a greater handicap
^29^. The THI is widely used as the primary outcome measure in double-blind trials with a control group to assess the effect of pharmacological or non-pharmacological agents in tinnitus patients. The functional subscale items reflect the effect of tinnitus on mental, social, occupational, and physical functioning. The emotional subscale items probe the individual’s emotional reactions to the tinnitus and the catastrophic response items address whether tinnitus makes the respondent feel desperate, trapped, hopeless or out of control. In this study, the THI will be assessed prior to intervention, and immediately, and at one month after the last tDCS session. Response to treatment is defined as a reduction of equal or more than 20 points in THI score (Pre-treatment THI – Post-treatment THI ≥ 20). This cut-off value for treatment response to tDCS is generally considered as significant clinical improvement in the previous similar studies
^15,
30^. 

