## Abstract

**Background**: Transcranial Direct Current Stimulation (tDCS) is reportedly a potential treatment option for chronic tinnitus. The main drawbacks of previous studies are short term follow up and focusing on the efficacy of single session tDCS. This study aims to investigate the therapeutic efficacy, adverse effects (AEs) and tolerability of repeated sessions of bilateral tDCS over auditory cortex (AC) on tinnitus symptoms

**Methods**: This will be a double-blinded randomized placebo controlled parallel trial on patients (n=90) with intractable chronic tinnitus (> 2 years) randomly divided into three groups of anodal, cathodal, and sham tDCS. In the sham treatment, after 30 sec the device will be turned OFF without informing the patients. The tDCS protocol consists of 10 sessions (daily  20 min session; 2 mA current for 5 consecutive days per week and 2 consecutive weeks) applied through 35 cm
^2^ electrodes. The primary outcome is tinnitus handicap inventory (THI) which will be assessed pre- and post-intervention and at one month follow-up. The secondary outcomes are tinnitus loudness and distress to be assessed using a visual analogue scale (VAS) pre-intervention, and immediately, one hour, one week, and one month after last stimulation. The AEs and tolerability of patients will be evaluated after each session using a customized questionnaire. Possible interactions between the disease features and treatment response will be evaluated.

**Discussion**: To our knowledge this is the first study to investigate the effects of repeated sessions of tDCS on chronic tinnitus symptoms with one month follow-up. In addition, the AEs, and tolerability of patients will be studied. In addition, the possible interactions between the disease specific features including the hearing loss, laterality, type of tinnitus, and treatment response will be evaluated.

**Trial registration**: The study has been registered as a clinical trial in Iranian Registry of Clinical Trial (
IRCT2016110124635N6) on the 01/06/2017.

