21^. The main hypothesis for therapeutic application of tDCS in tinnitus is disturbing ongoing abnormal neural activities responsible for tinnitus. According to this approach, the areas involved in the pathophysiology of tinnitus are targeted by tDCS. The other hypothesis of eliciting therapeutic outcomes from tDCS is inducing plastic changes to alter the maladaptive plasticity of the involved regions. The important point for treatment of tinnitus is that there is a large network consisting of different auditory and non-auditory regions with overlapping functions
^22–
24^.

Most of the studies performed to date, have focused on the effects of single tDCS session on tinnitus symptoms, with short term follow ups ranging some hours to some days. To our knowledge, there is no published study investigating the effect of repeated sessions of tDCS over the auditory cortex (AC) on tinnitus symptoms as well as the AEs of and tolerability to the tDCS with one month follow up. This study aims to investigate the effects of repeated sessions of tDCS on tinnitus symptoms with one month follow-up. Our main hypothesis is that repeated sessions will lead to aggregative therapeutic effects on tinnitus. In addition, we want to evaluate possible association between treatment response, and patient's and tinnitus specific characteristics including gender, THI basal score, laterality, tinnitus quality, duration, hearing loss class, etc.

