### Adverse effects and tolerability

The previous studies on the safety and tolerability of tDCS have shown that the 2 mA current applied in 20 minutes are associated with no serious AEs
^24,
26^. The common reported AEs are itching or tingling sensation, mild headache or fatigue and local burns at the site of stimulation. However, most of the AEs and tolerability assessments have been performed on the tDCS were for single session ranging 20–30 minutes and current of 1 to 2 mA. In our study, we will use repeated sessions of tDCS (2 mA current for 20 minute, total 10 sessions, daily one session, five consecutive days per week and 2 consecutive weeks), thus the reported AEs in the previous studies may be intensified. Therefore, we will assess the AEs using a customized questionnaire (
Supplementary File 1). The questionnaire will be performed during and after each tDCS session to record all the perceived AEs from the patients in all three tDCS groups.

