***Adverse effects and tolerability***

Previous studies have reported no severe AEs of tDCS for different protocols. However, most of the previous studies used single session tDCS. For this study, considering the multisession protocol of tDCS, the AEs of and tolerability to the repeated sessions of tDCS will be assessed using a customized questionnaire (
Supplementary File 1) which will be applied after the last session.

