Finally, we will examine the number of responders versus non-responders under each treatment condition (anodal, cathodal, and sham). This will be accomplished by calculating change scores between the pre-treatment and post-treatment THI values (Pre-treatment – Post-treatment). Responders will be considered individuals who showed reductions in THI score of equal or more than 20 points in the THI score (Pre-treatment THI – Post-treatment THI ≥ 20). For tinnitus loudness and distress a 10 percent or 2-point reduction of 0–10 scale is considered as treatment response. Pearson’s chi-square tests will be used to evaluate whether there are differences in the proportion of responders versus non-responders under each condition. For all statistical tests the P-value < 0.05 is defined as statistically significant level.

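### Every stated schedule for adverse effects ends at the last session, although the Background counts adverse effects with one-month follow-up as part of the gap the trial fills

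*Protocol article*

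**What the plan says.** The Abstract gives the aim: "This study aims to investigate the therapeutic efficacy, adverse effects (AEs) and tolerability of repeated sessions of bilateral tDCS". The Background, describing what earlier work lacks, names effects on symptoms, "as well as the AEs of and tolerability to the tDCS with one month follow up".

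The protocol article gives the timing of AE collection in four places:

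- Abstract, Methods: "The AEs and tolerability of patients will be evaluated after each session using a customized questionnaire".
- Adverse effects and tolerability, the section that follows the stimulation protocol: "The questionnaire will be performed during and after each tDCS session to record all the perceived AEs".
- The second section of that title, after Blinding assessment: a questionnaire "which will be applied after the last session".
- Outcomes assessments, Table 2: the row "AEs and Tolerability" carries one mark, at T2.

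The footnote to Table 2 defines the later times: "T _2_: immediately after last session, T _3_: at hour after last session, T _4_: one week, and T _5_: at month after last tDCS". The same table marks loudness and distress at T2 to T5, and THI at T1, T2 and T5.

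Statistical assessments plans a mixed repeated-measures ANOVA of THI, loudness and distress. It then adds a two-way split: "Finally, we will examine the number of responders versus non-responders under each treatment condition (anodal, cathodal, and sham". A responder is a patient whose THI falls by at least 20 points; everyone else is a non-responder.

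**The concern.** The article's own safety reasoning makes the gap matter. Its first AE section says that most earlier safety data come from single sessions and that ten sessions might make AEs worse. It lists mild headache, fatigue and local burns among the known effects. These can begin or persist after a patient has left session 10. If no one asks at one week or one month, they enter the results only if a patient happens to mention them. A report of good tolerability over the follow-up would then rest on no planned observation after treatment ended.

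A smaller issue lies next to this. In the responder table, a patient whose THI rises by 20 points is counted with one whose THI does not move, so the planned summaries give no number of patients who got worse.

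**Working it through.** The documents give no figure to reproduce on this point. The check traces the schedule and then sizes the gap.

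**1. Coverage after T2.** The time points after T2 are T3, T4 and T5.

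| Measure | Assessed at T3–T5 |
|---|---|
| Loudness, distress | 3 of 3 |
| THI | 1 of 3 (T5) |
| AE questionnaire | 0 of 3 |

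Under the Abstract and the first AE section, the last AE record is made after session 10, which is T2. Under the second AE section and Table 2, T2 is the only record. The stimulation rows of Table 2 show no marks in the text available, so a graphic spanning the treatment period may have been lost. That could affect the treatment column, but all three prose statements also stop at session 10.

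**2. Share of time not covered.** Assume a two-day break between the two five-day blocks, so that treatment spans 5 + 2 + 5 = 12 days, and a month of 30 days. The uncovered share is 30 / (12 + 30) = 71%. This is calendar time, not a share of AE risk.

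**3. What asking at T5 would give.** With zero late AEs among n patients, the one-sided 95% upper bound on the rate is 1 − 0.05^(1/n). The Sample size calculation gives 25 per group; the 90 patients stated elsewhere, allocated 1:1:1, give 30. Both are shown.

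- One arm: 11.3% at n = 25; 9.5% at n = 30.
- Both active arms pooled: 5.8% at n = 50; 4.9% at n = 60.

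The chance of seeing at least one late AE in the pooled active arms is 1 − (1 − p)^n. For assumed true rates p of 1%, 2% and 5% it is 39%, 64% and 92% at n = 50, and 45%, 70% and 95% at n = 60. Without the question, no such bound exists.

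**4. Tinnitus worsening.** THI runs from 0 to 100, higher being worse, and change is computed as pre minus post, so a worsening is recorded with its sign. Using a normal approximation at two-sided 5% and assumed SDs of 15 to 25 points, power for a between-group difference in THI is:

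- 20 points: above 99% down to 81% at 25 per arm; above 99% down to 87% at 30.
- 10 points: 65% down to 29% at 25 per arm; 73% down to 34% at 30.

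A large group-level worsening would therefore be seen. Worsening in a minority could be missed. As a hypothetical case, let 20% of an arm worsen by 20 points and 80% improve by 10. The mean change is 0.8 × 10 − 0.2 × 20 = 4 points of improvement, and all patients are non-responders. Neither planned summary would show that one in five got worse.

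**The case against.** The Background phrase is ambiguous. The month of follow-up closes a long sentence and may describe the study as a whole. The next sentence attaches it to symptoms only. The Abstract and the Discussion also state the one-month novelty for symptoms or for the study, and mention AEs separately. Both AE sections justify data collection by the number of sessions, not by late effects. This stands as a reason for caution: no passage expressly plans a tolerability result at one month. It does not remove the mismatch, because the sentence as written covers AEs, and rewording it is one of the two remedies.

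Supplementary File 1 and the full protocol are not shown, and unsolicited reports at T4 or T5 may be handled there. A reader might infer that late AEs would never be counted. The documents do not support that; they establish only that no questionnaire is scheduled after T2. The timing itself is not a detail lost in condensing, because the article sets it out in Table 2 and leaves those cells empty while filling them for other measures.

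A reader might also infer that tinnitus-related harm cannot be seen. That is not supported either. THI at T5 and loudness and distress to T5 are recorded and analysed as continuous scores, so worsening is in the data and visible in group means. A count of patients who worsen is a useful supplement, commonly left to an analysis plan; its absence is not an error.

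Finally, many of the listed AEs are short-lived or local to the electrodes, so the 71% overstates the share of AEs likely to be missed.

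**Conclusion.** The point holds in limited form. AE collection stops at T2 under all four statements, while the Background claims AEs and tolerability with one-month follow-up as part of the trial's contribution. The schedule leaves three later time points, and about 71% of the time from first session to T5, without a planned AE question. This rests on a 12-day treatment span, a 30-day month, and the article's schedule matching that of the full protocol. The efficacy analyses are unaffected. What lacks support is any statement about tolerability beyond the stimulation period.

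The disagreement between the four statements is a separate, plain contradiction. It decides whether there are at least ten AE records per patient or one.

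**What to change.** 1. Reconcile the timing of AE collection across the Abstract, both sections titled Adverse effects and tolerability, and Table 2, so that all four say the same.
2. Add the existing questionnaire at T4 and T5. Have it ask about the time since the previous contact, and have it completed after the THI and VAS ratings so that the AE questions cannot influence them.
3. If step 2 is not adopted, reword the Background so that the claim on AEs and tolerability is limited to the stimulation period.
4. Optionally, report by arm the number of patients whose THI has risen by 20 points or more at T5. This mirrors the article's own response threshold and uses data already collected.

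The cost is a few minutes of patient time at two assessments already scheduled, and one table row if step 4 is taken up. Sample size and the planned efficacy tests do not change.

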***Secondary outcomes***

**Tinnitus loudness and distress**. The tinnitus loudness and distress will be assessed using a numeral 0–10 visual analogue scale rating scale before intervention, and immediately, one hour, one week, and one month after last tDCS session. For tinnitus loudness and distress a 10 percent or 2 point reduction of 0–10 scale will be considered as treatment response
^31,
32^.

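### The loudness and distress response rule joins two different thresholds: on a 0–10 scale, 10 percent is 1 point and 2 points is 20 percent

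*Protocol article*

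**What the plan says.** The Secondary outcomes section says that loudness and distress are "assessed using a numeral 0–10 visual analogue scale rating scale before intervention" and at four later times: immediately, one hour, one week and one month after the last session (T2 to T5). It then gives the rule: "For tinnitus loudness and distress a 10 percent or 2 point reduction" on the 0–10 scale counts as response.

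Statistical assessments repeats it almost word for word: "For tinnitus loudness and distress a 10 percent or 2-point reduction of 0–10 scale is considered as treatment response". In the same paragraph the responder classification goes into a test: "Pearson’s chi-square tests will be used to evaluate whether there are differences in the proportion of responders versus non-responders under each condition".

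The primary outcome is handled differently, with a single threshold: "Response to treatment is defined as a reduction of equal or more than 20 points in THI score", on a total that runs from 0 to 100.

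The article does not say whether the 10 percent refers to the scale or to the patient's own baseline, beyond naming the 0–10 scale after both criteria. It does not say whether *or* means that either suffices or that the two are equivalent. It names no post-treatment time point for loudness or distress response.

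**The concern.** A responder definition has to sort each patient one way only. Here two thresholds that differ by a factor of two stand side by side as if interchangeable, and nothing else in the article reconciles them. Because the rule appears in both the outcome and the statistics sections, it is unlikely to be a slip in one place.

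Taken literally, the looser criterion always decides and the 2-point figure does no work. Taken as a restatement, the rule is arithmetically false. In either case the person who codes the analysis must settle what the article leaves open, for two outcomes. If that is done after the data are seen, the reported responder rates can be moved by the choice of reading.

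**Working it through.** **Inputs from the article.** Scale 0 to 10 (Secondary outcomes). Response criteria 10 percent or 2 points (Secondary outcomes; Statistical assessments). THI response 20 points on a 0–100 total (Outcomes assessments).

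**Step 1. Put the criteria on one scale.**
- 10 percent of the range: 0.10 × 10 = 1 point.
- 2 points as a share of the range: 2 / 10 = 20 percent.
- THI for comparison: 20 / 100 = 20 percent of the range.

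The article's two figures do not reproduce each other. The 2-point figure matches the THI rule as a share of range; the 10 percent figure is half of it.

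**Step 2. Read *or* as either suffices.**
- *Percent of scale:* the threshold is 1 point. Any drop of 2 points already exceeds it.
- *Percent of baseline:* the threshold is b/10 for baseline b. It is 0.1 at b = 1, 0.5 at b = 5 and 1.0 at b = 10, so never above 1 point. A 1-point drop is 100/b percent of baseline: 100% at b = 1, 20% at b = 5, 10% at b = 10.

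All possible pairs of baseline and drop were enumerated under both bases: 55 pairs on whole numbers and 5,050 in steps of 0.1. In none does a drop meet the 2-point criterion without also meeting the 10 percent criterion, and no drop of 1 point or more fails to be a response. With percent of baseline and fractional ratings, drops below 1 point also count at any baseline under 10.

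**Step 3. Read *or* as a restatement.** Then 10 percent would have to equal 2 points; by Step 1 it equals 1. The rule contradicts itself.

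**Step 4. How far the readings differ.** The article gives no SD of change, so this is an illustration. Assume no true change and a normally distributed change with SD s of 1.0, 1.5 or 2.0 points, ignoring the ends of the scale. On a continuous scale, P(drop ≥ c) = 1 − Φ(c/s). For ratings rounded to whole numbers, P(drop ≥ c) = 1 − Φ((c − 0.5)/s).

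| s | Whole numbers, 1 point | Whole numbers, 2 points | Continuous, 1 point | Continuous, 2 points |
|---|---|---|---|---|
| 1.0 | 31% | 7% | 16% | 2% |
| 1.5 | 37% | 16% | 25% | 9% |
| 2.0 | 40% | 23% | 31% | 16% |

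The whole-number columns hold for either base of the percentage. The continuous 1-point column takes the percentage as of the scale; as percent of baseline, the rates would be higher.

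**Step 5. Effect on a contrast.** Take whole-number ratings, s = 1.5, one arm with no change and one with a true mean drop of 1 point. In the second arm, P(drop ≥ 1) = 1 − Φ((0.5 − 1)/1.5) = 63% and P(drop ≥ 2) = 1 − Φ((1.5 − 1)/1.5) = 37%.
- 1-point rule: 63% − 37% = 26 percentage points.
- 2-point rule: 37% − 16% = 21 percentage points.

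**The case against.** **The looser rule harms the comparison.** A reader might infer that counting more chance responders must blur the difference between active and sham stimulation. Step 5 shows otherwise: in that scenario the gap in response rates is larger under the 1-point rule (26 against 21 points). Only the ratio of rates favours the 2-point rule. What stands is that absolute rates rise in every arm.

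**One point is the smallest step on the scale.** That needs whole-number ratings. The article calls the instrument both numeral and visual analogue, which does not settle it. On a continuous scale 1 point is not the smallest change, and the chance rates are lower. Both sets of figures are therefore given.

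**The rule is clear: either suffices.** If so, and ratings are whole numbers, nothing is left to choose afterwards. The risk of a choice after the data are seen exists only because the wording also admits the other reading, or a different base on a fractional scale. That is fair, but the literal reading leaves a 2-point figure that can never apply, which is itself a sign that the text does not say what was meant.

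**The intended threshold is obviously 2 points.** The match with the THI rule points that way but does not prove it. The article supports the rule with two references that are not at hand, and the investigators may have meant 10 percent.

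**It is minor.** Loudness and distress are also analysed as scores by mixed repeated-measures ANOVA, which the rule does not touch. The THI rule has one threshold, and the sample size calculation does not use the loudness and distress rule. This stands and limits the weight of the point.

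**Conclusion.** The rule is defective as written under each reading examined: one criterion is redundant, or the two contradict each other. That conclusion rests on arithmetic alone and needs no assumption about the data.

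The size rests on assumed values. With no true change and an SD of change of 1 to 2 points, the share labelled responders is about 31–40% at 1 point against 7–23% at 2 points on whole-number ratings, or about 16–31% against 2–16% on a continuous scale with the percentage taken of the scale. The reported rates in all three arms, sham included, thus depend materially on the reading. The documents do not support a claim that the contrast between arms is weakened, nor do they show which threshold was intended.

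This should be fixed, but it is confined to the responder counts and chi-square tests for two secondary outcomes. The THI primary outcome, the ANOVAs on scores and the sample size are unaffected.

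**What to change.** Before any data are analysed, replace the phrase in both Secondary outcomes and Statistical assessments with one threshold, the base it is measured against, and one named post-treatment time point. State also whether ratings are whole numbers or continuous.

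A reduction of at least 2 points from T1 (20% of the scale) would be consistent with the THI rule of 20 out of 100 points, but the investigators must confirm which threshold they meant. The time point cannot simply be borrowed from the THI: its response rule says only post-treatment, and the THI is measured after treatment at both T2 and T5. One of the four post-treatment assessments of loudness and distress has to be chosen explicitly.

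The cost is one sentence in two places. Trial status reports that allocation had not yet taken place, so the change could be made without sight of outcome data. If 2 points is chosen, the reported responder rates will be lower than under the 1-point reading.
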